### **Data collection procedures**

The participants will be evaluated at the following times: The first evaluation will be performed after 48 hours of admission to the ICU. The second assessment will take place from the 30th day after hospital discharge during the outpatient reassessment and the third assessment will take place at 90 days after hospital discharge to repeat MRI. The evaluative tests performed in each of the stages are described in the timeline described in Figure 3.

## Anamnesis and clinical-physical evaluation

Initially, an interview will be held with the volunteer, where the clinical-physical evaluation form will be filled out (Appendix A), containing data regarding the identification of participants, personal and family pathological history, complaints, lifestyle habits, medications used, previous procedures, admission exams (Biomarkers, Electrocardiogram-ECG, Transthoracic echocardiogram-TEE, and Heart Catheterization- HEART CATH); In addition to physical assessment with data collection of vital signs and anthropometric data.

[figure not shown]

**Fig. 3** – Timeline of assessments

## Physical Fitness analysis

### *Cardiopulmonary exercise test (CPET)*

The maximum incremental test of the type Cardiopulmonary Exertion Test (CPET) or Ergospirometric Test will be used to measure functional capacity through ACR (Analysed by VO2

value) after CR. Patients will perform CPET on a treadmill (Centurion 300 model, Micromed, Brazil) conducted under the incremental load protocol previously developed by Weber so that exhaustion occurs between 8 and 12 minutes through the ErgoPC Elite test system (Micromed, Brazil), and all will perform the same protocol (Ramp). As part of the test, patients will be monitored by a 12-lead electrocardiogram at rest (Digital ECG, Micromed, Brazil), (SpO2) will be monitored using a Nonin 2500 oximeter. subjective perception of exertion monitored, using the Borg scale (51) as an instrument. All procedures will be performed under medical supervision and patients will be authorized to perform the test while leaning on the front support bars of the treadmill.

The metabolic gas analyzer Cortex Metamax 3B (Germany) and the Metalyzer 3B software will be used to capture, analyze, and interpret expired gases. The system consists of breath-by-breath monitoring, using a silicone mask with a 45ml dead space, where a volume turbine is coupled to measure minute volume (VE), and a gas line connected to an oxygen and oxygen cell. carbon dioxide for reading VO2, and VCO2, respectively. The system allows the transmission of data to the software, allowing the real-time monitoring of VO2 measurements relative to body mass (VO2/Kg), minute ventilation (VE), respiratory exchange rate, the ventilatory equivalent of carbon dioxide ( VE/VCO2) and oxygen (VE/VO2), and the oxygen pulse. The gas analyzer will be calibrated daily. The silicone mask with the turbine and gas line will be attached to the volunteer before the start of the test, and a period of two minutes will be respected allowing adaptation to the mask, avoiding capture of hyperventilation measures. Then the participant will remain in an orthostatic position at rest for two minutes to measure the baseline VO2 and respect the VE, R, and VO2 suitable for starting the test. The ideal VE at rest to start the exercise is between 8 and 15L/min, the R between 0.75 and 0.85, and the VO2RESO close to 3.5mL/kg/min, corresponding to 1 MET.

Participants will be instructed to perform the test until such time as they feel unable to continue. Throughout the test, cardiorespiratory and metabolic measurements will be recorded. The 12-lead electrocardiogram will be continuously monitored and will provide heart rate values. Blood pressure will be measured using a mercury column sphygmomanometer at two-minute intervals, peripheral oxygen saturation (SpO2) will be continuously monitored through the Nonin 2500 oximeter, and subjective exertion will be collected at two-minute intervals and at exhaustion (2). Criteria for stopping testing will be strictly followed according to the ATS 2003

standardization (52). The CPETs will be performed at the Cardiac Rehabilitation Unit of the Hospital Universitário Onofre Lopes (CORE-HUOL) (Figure 4) which has controlled room temperature and equipment and medications needed to provide emergency care. The silicone mask with the turbine and gas line will be attached to the volunteer before the start of the test, and a period of two minutes will be respected allowing adaptation to the mask, avoiding capture of hyperventilation measures. Then the participant will remain in an orthostatic position at rest for two minutes to measure the baseline  $\text{VO}_2$  and respect the  $\text{VE}$ ,  $\text{R}$ , and  $\text{VO}_2$  suitable for starting the test. The ideal  $\text{VE}$  at rest to start the exercise is between 8 and 15L/min, the  $\text{R}$  between 0.75 and 0.85, and the  $\text{VO}_{2\text{RESO}}$  close to 3.5mL/kg/min, corresponding to 1 MET.

After the end of the test, the patient remains monitored for five minutes to check the metabolic and cardiorespiratory behavior during recovery, with three minutes of active recovery and two minutes of passive recovery. After this period, new measurements of BP,  $\text{SpO}_2$ , and Borg were performed.

If some of the tests need to be interrupted due to patient discomfort (fatigue, dyspnea, dizziness), the patient will receive the necessary care for his recovery. On the days when the maximum effort tests are carried out, patients will be assisted by a cardiologist in a hospital environment and, if necessary, appropriate support will be offered to the patient, such as a 5 to 10-minute rest, monitoring of vital signs and even referral to a sector of the hospital with oxygen therapy and greater therapeutic support, according to the clinical evaluation carried out by the physician present.

[figure not shown]

**Fig. 4 – Cardiac rehabilitation unit – CPET (CORE-HUOL).**

### *30 second chair sit-to-stand test - 30CST*

The 30-second chair sit-to-stand test is a submaximal test indicated and validated for more debilitated individuals such as the elderly or hospitalized patients (30,31). In order to carry out the test, we will use, in accordance with previous studies and standardized recommendations, a rigid chair, with a standard height of 45cm and without armrests. The patient will be instructed to perform as quickly as possible in a time of 30 seconds the movement of sitting and standing up from the chair, which will be accounted for by the evaluator. The 30CST will be performed in 2 moments: At ICU discharge and 30 days after hospital discharge in both study groups.

The assessment of the intra- and inter-examiner reliability of the 30s TSL in post-AMI patients will be carried out from the recording of participants performing the TSL30s and evaluators previously selected to score the filmed tests. The total sample of 24 participants will be evaluated. The test will be administered by the principal investigator who will be blinded to the allocation of participants to study groups. Ten evaluators will be recruited from the hospital's team of physiotherapists from the ICU units and wards. All raters will be previously trained by the principal investigator before the assessments. After performing and filming the tests at ICU discharge (First assessment), the filmed tests will be presented to the evaluators who will score

each test. After 30 days, the same filmed tests will be presented again to the same evaluators for reassessment.

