### **Secondary objectives**

- To assess the variation in functional capacity by measuring cardiorespiratory fitness after in-hospital CR, using maximum VO2 (maximum oxygen consumption) as a result measure;
- To analyze the dose of aerobic training provided to patients in in-hospital CR and its impact on the outcome of functional capacity;
- Relate the standard method of measuring VO2, the cardiopulmonary test, to a submaximal evaluation method, the 30s sit-to-stand test, evaluating its validity and reproducibility;
- Observe the influence of early CR on the morphological parameters of ventricular remodeling through nuclear magnetic resonance (NMR);
- Investigate heart rate variability after early cardiac rehabilitation.
- Identify the rate of adverse events and the safety level of the protocol evaluated in this clinical trial;

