In step 2, patients will follow early exercise-based cardiac rehabilitation performed following all prescription parameters (FITT-VP) and safety criteria recommended by ACSM, 2018 (33). The institutional protocol (**Appendix B**) will be performed with a **frequency** of 2 sessions per day, during the entire hospitalization, with an average of 8 to 10 total sessions; Low **intensity** for aerobic training with METs estimated by the subjective perception of effort of BORG between 9 to 12 reaching between 2 to 3 METs and for resistance training with 2 to 3 series of 60% of the maximum repetitions reached in the 30s sit-to-stand test; **Type** of exercises involved will be aerobic training using the cycle ergometer associated with resistance training using the body's own weight with functional sit-to-stand training; Aerobic training **time** ranging from 3 to 20 minutes. The **Volume or Dose** of aerobic training will be measured by calculating the training dose per session and the total dose applied during hospitalization, providing a value in time x intensity (METs) x frequency of accumulated sessions and total number of sessions x time. The structured **progression** in the protocol focuses on the time of aerobic exercise and the number of series of resistance training. The exercise sessions will follow the protocol presented, however, present individualized prescriptions based on tolerance time during aerobic training with a cycle ergometer and resistance training from the maximum number of repetitions reached in the 30s TSL evaluated

individually before randomization.

Before hospital discharge, patients in the intervention group will receive an exercise guidance booklet (Appendix C) to perform step 3 of semi-supervised and continued cardiac rehabilitation with the exercise time reached at the end of in-hospital rehabilitation, frequency of 5 x per week and progression of 5 minutes each week within the first month after hospital discharge, according to tolerance and self-monitoring of intensity through perceived exertion using the Borg scale, maintained between 9 to 12, to ensure light exercise to moderate intensity. In this phase, patients in the intervention group will be monitored weekly by telephone and will receive a diary (Appendix C) to record the time of daily and weekly activity that they must deliver when investigating when they return for reassessment 30 days after hospital discharge.

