## **Statistic Strategy**

The variables of interest will be analyzed using the software (Graph Pad Prism version 7.0) and initially evaluated for the normal distribution of data using the Shapiro-Wilk test considering  $n < 30$ . In the case of data with normal distribution, they will be analyzed for the mean and standard deviation. Data without normal distribution will be analyzed for median and percentiles. Comparison analyses of the physical functional variables of the 30CST, MRI morphological variables, and HRV cardiac functional variables of the PRE-CR and POST-CR times of each group will be performed using the Wilcoxon test if the data were non-parametric and the paired t-test if the data were parametric. Comparison between the control and intervention groups for CPET will be performed using the independent t-test or the Mann-Whitney test, depending on the normality of the data. The reliability and validity of the 30CST will be analyzed using Spearman's correlation and the intra-examiner reliability coefficient. For all hypothesis tests, a significance of 5% probability ( $P < 0.05$ ) of error will be assigned.

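### Reproducibility of the 30CST is assessed only by re-scoring films, while the repeat test at 30 minutes on the data form is neither described nor analysed in the text

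*Protocol*

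**What the plan says.** - **Objective** (Protocol, Secondary objectives): the 30CST is to be related to the cardiopulmonary test, "evaluating its validity and reproducibility".
- **Occasions** (30CST section): "The 30CST will be performed in 2 moments: At ICU discharge and 30 days after hospital discharge in both study groups". No second trial within an occasion is mentioned.
- **Source of the reliability data** (same section): the intra- and inter-examiner assessment "will be carried out from the recording of participants performing the TSL30s and evaluators previously selected to score the filmed tests". Ten physiotherapists score the films made at ICU discharge, and all 24 participants are to be evaluated. Then: "After 30 days, the same filmed tests will be presented again to the same evaluators for reassessment".
- **Analysis** (Statistic Strategy): "The reliability and validity of the 30CST will be analyzed using Spearman's correlation and the intra-examiner reliability coefficient". The 30CST is also compared before and after rehabilitation within each group.
- **Data form** (Appendix A, Physical tests): four entries, labelled 30CST (1), (1 + 30min), (2) and (2 + 30min). Each has its own result, adverse-event field and vital signs.

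**The concern.** Reproducibility of a performance test has two parts: whether examiners count the same performance alike, and whether the patient gives the same performance again. The plan as written covers only the first. In a test of maximal speed over 30 seconds, in patients a few days after infarction, the second part is where practice or fatigue would show.

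The introduction says that no trial has yet evaluated the validity and safety of this test in patients hospitalised after infarction, so the measurement results are meant as a contribution of the study. A high examiner coefficient could then be reported as evidence that the test is reproducible in these patients, which it would not be. The form already has room for the data that would settle this, and the plan gives those data no purpose.

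**Working it through.** The plan states no figure on this point, so there is none to reproduce. The check sets the sections side by side and asks what each set of data can estimate.

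**Counts**

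- Text: 2 occasions, no repeat described.
- Form: 2 occasions x 2 trials = 4 results per patient. With 24 patients this is up to 24 x 2 = 48 pairs taken 30 minutes apart, 24 of them at ICU discharge.
- Film study: 24 participants x 10 evaluators x 2 scorings = 480 scores, assuming one film per participant. They describe 24 performances, and no participant contributes a second one.

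**What each can estimate**

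Write a recorded score as the patient's usual level (variance A between patients), plus the deviation of that particular performance (variance B), plus counting error (variance C).

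- *Same film, same examiner, scored twice.* Level and performance are fixed. The difference has variance 2C and the coefficient is (A + B) / (A + B + C). B counts as true signal. If counting is perfect (C = 0), the coefficient is 1 whatever the size of B. Using several examiners adds differences between them but leaves the performance fixed.
- *Two performances 30 minutes apart.* The difference has a mean equal to the practice or fatigue effect and variance 2(B + C). With no such effect the coefficient is A / (A + B + C). An absolute-agreement coefficient is lower still when there is a shift.

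The film coefficient therefore cannot be below the test-retest coefficient under this model, and it carries no information on B or on practice.

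**Could another planned analysis fill the gap?**

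- ICU discharge against 30 days after hospital discharge: no, because recovery and the intervention lie between the two.
- Spearman's correlation: even applied to the repeat pair, it would miss a practice effect. If every patient gained exactly 1 repetition, the ranks would be unchanged and the correlation would be 1.
- The film analysis: no, as shown above.

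The first-versus-30-minute pair is the only source in the document that addresses test-retest reproducibility. Neither the 30CST section nor Statistic Strategy mentions it.

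**The case against.** **The text does not contradict the form.** A reader might infer that the text permits one test per visit. It does not say so: two moments fixes the occasions, and two trials can fall within each. The text is silent on the repeat. The form is also not an exact specification, since it has two lines for cardiac resonance while the text plans a baseline scan and two follow-ups. This objection stands, and it is why the request is to reconcile the two and not to correct a false statement.

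**Examiner agreement is part of reproducibility.** This also stands. The film study is a sound design for what the 30CST section calls it. What remains is that it covers only part of the objective.

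**Which trial is the analysed value can be left to an analysis plan.** This stands too. A reader might infer that the open choice inflates the false-positive rate of the before-after test. That happens only if the rule differs between visits. As an illustration, take n = 12, a two-sided 5% paired t-test, no true change, a measurement SD of 0.5 to 1.5 repetitions and an SD of individual change of 1 to 2 (all SDs assumed). In 20,000 simulated trials per setting, the first test before and the better of two after gave:

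| Practice effect (assumed) | False gain, repetitions | Type I error |
|---|---|---|
| none | 0.28 to 0.85 | 7% to 23% |
| 1 repetition | 1.02 to 1.45 | 33% to 76% |

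First-first and best-best stayed at 4.7% to 5.2% throughout. No section suggests an asymmetric rule, so these figures describe something the protocol does not plan. The phrase "resistance training from the maximum number of repetitions reached in the 30s TSL evaluated" concerns the training prescription and does not settle the outcome value either way.

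**Nothing says the second result is discarded.** A reader might infer that precision is being thrown away. The documents do not say what happens to the second result, so that claim has no support.

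**Conclusion.** The point holds in a limited form. The reproducibility objective is served only by intra- and inter-examiner scoring of the same films, which shows counting agreement and cannot show patient test-retest reproducibility or a practice effect. The form records a repeat that would show both, and the methods text gives it neither a description nor an analysis.

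The severity is minor. One secondary objective is affected; the sample size rests on VO2, and the between-group comparison on the cardiopulmonary test is untouched. The conclusion needs no assumed variance: it follows from the fact that a film holds the performance fixed. It does assume that the form's 30-minute entries reflect a test the investigators intend to do, which only they can confirm. An analysis plan, if one exists, may already name the missing analysis, but the gap between the form and the methods text lies within this document.

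**What to change.** State in the 30CST section whether the test at 30 minutes is done, and make the section and Appendix A agree.

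**If it is done:**

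- Analyse the first against the 30-minute result as test-retest: absolute-agreement intraclass correlation, mean difference, standard error of measurement and 95% limits of agreement. Make the ICU-discharge pair the main analysis; all 24 participants can contribute, and the baseline test is placed before randomisation.
- Describe the film study as examiner reliability only.
- Fix one rule for the 30CST value, the same at both visits and in both arms. First, best or mean would each serve.

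**If it is not done:** remove the two 30-minute fields and narrow the secondary objective to examiner reliability.

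The cost is a few sentences in the 30CST section and Statistic Strategy, or two deleted form fields and a reworded objective. Neither route needs data beyond what the form already provides for.

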### Cardiac morphology and function analysis

#### Cardiac morphology

Cardiac nuclear magnetic resonance (NMR) can be used for several important evaluations after acute myocardial infarction. MRI allows the diagnosis of myocardial infarction in its acute or chronic condition, provides several prognostic indicators that can impact the risk stratification of patients, in addition to allowing the identification of complications after AMI, such as aneurysm, pericarditis, and thrombi among others (53). The evaluation of the extent of scarring after AMI is a valuable predictor of therapeutic success, being used as a common endpoint in clinical trials. The extent of infarction is inversely related to clinical prognosis and is a more sensitive predictor than mass and ventricular ejection fraction of ventricular tachycardia, ultimately predicting all-cause mortality and ejection fraction-independent survival (53).

In this study, standard protocols will be used to assess cardiac morphology and function, such as end-systolic and diastolic volumes and ventricular ejection fraction evaluated through the CINE SSFP sequence, in addition to the delayed enhancement sequence with gadolinium (53). The exam will be performed at baseline, still during hospital stay, around the fourth to sixth day after the AMI and in two follow-up moments, the first one from 4 weeks after the event, with a tolerance of up to 2 weeks for image and the second from 3 months after the event with a tolerance of two weeks.

The technique used to evaluate the scar extension will be the delayed enhancement with the administration of gadolinium chelate. The patient will receive the gadolinium chelate between 10 and 20 minutes before the exam. In the presence of scar tissue, there is an increase in the extracellular space in relation to the intracellular environment due to the rupture of the cardiomyocyte membranes, with greater gadolinium impregnation in this region, generating hyper-enhancement in the image (53). Scar size assessment will use the following semi-quantitative method: Visual scoring of 17 standardized areas, on a 5-point scale, where 0= no hyperenhancing, 1= 1-25%, 2= 26 – 50%, 3=51

– 75% and 4= 76 – 100% hyperenhancing. The total scar score is given by adding the

scores for each segment and dividing by 17 (53).

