### **Early cardiac rehabilitation program**

The early cardiac rehabilitation (CR) program based on physical exercise will be carried out in 3 steps (Step 1 - Functional mobilization; Step 2 - Early cardiac rehabilitation; Step 3 - Continued cardiac rehabilitation).

In step 1 of early mobilization, all patients in the control and intervention groups, after 8 hours of clinical stability (absence of ischemic signs and symptoms) will perform mobility increment exercises to ensure functional mobility until discharge from the ICU, as per step 1 of the in-hospital CR protocol in (Appendix B). After ensuring functional mobility, patients will be randomized to control or intervention groups. Both groups will perform steps 1 to STEP 3 of the early CR protocol, with the physical activity is a free-demand ambulation in addition to standardized drug treatment, however, only the intervention group will proceed to STEP 4 of steps 1 and steps 2 and 3 from early and continued cardiac rehabilitation.

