|          |                                                                     |                                                                                                                                |                                         |                    |           |
|----------|---------------------------------------------------------------------|--------------------------------------------------------------------------------------------------------------------------------|-----------------------------------------|--------------------|-----------|
|          |                                                                     |                                                                                                                                |                                         |                    |           |
| 4 | Maintenance of the clinical picture and conditions specified above. | Aerobic: lower limb cycle ergometer on armchair + walking (75 to 100 meters).

Muscular endurance: sitto stand exercise. | 9-15min

2 x 60% test repetitions | Borg 9-10 (2 METs) | 30MET-min |

Subtitle: The frequency of the STEPS is twice a day following the established order. The progression of the exercises focuses on the exercise time, following the order of the STEPS. The aim of the protocol is to achieve an accumulated 90 MET-min until ICU discharge.

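### The day 4–6 baseline MRI is not tied to before randomisation and probably follows intervention-only sessions, yet it is analysed as PRE-CR; the timing of the first 30CST is also inconsistent

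*Protocol*

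**What the plan says.** **MRI.** The Cardiac morphology section states: "The exam will be performed at baseline, still during hospital stay, around the fourth to sixth day after the AMI". Follow-up scans come from about 4 weeks and 3 months after the event. Nothing in the text places the first scan before randomisation. The HRV section does set that condition for HRV.

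**Sequence of exercise.** Under Early cardiac rehabilitation program, all patients "after 8 hours of clinical stability (absence of ischemic signs and symptoms) will perform mobility increment exercises". Randomisation follows once functional mobility is ensured, with no day given. Both groups do STEPs 1–3, and then "only the intervention group will proceed to STEP 4 of steps 1 and steps 2 and 3 from early and continued cardiac rehabilitation". The frequency is "2 sessions per day, during the entire hospitalization, with an average of 8 to 10 total sessions". Appendix B repeats that STEPs run twice a day in order.

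**First 30CST.** Its own section says: "The 30CST will be performed in 2 moments: At ICU discharge and 30 days after hospital discharge in both study groups". The rehabilitation section says that the maximum repetitions are assessed "individually before randomization". Appendix B lists the test inside STEP 3 and sets the sit-to-stand load of STEP 4 as a percentage of the test repetitions.

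**General timing.** Data collection procedures adds: "The first evaluation will be performed after 48 hours of admission to the ICU".

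**Analysis.** The Statistic Strategy compares PRE-CR with POST-CR within each group for 30CST, MRI and HRV, by paired t-test or Wilcoxon test. It names a between-group comparison for CPET.

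**The concern.** A PRE-CR value should be taken before the treatment under test begins. If the intervention arm has already done sessions that the control arm does not do, the scan is an early on-treatment measurement in one arm only. Change measured from it leaves out whatever has already happened. This matters because the introduction justifies the morphology work by the lack of studies imaging the heart right after the in-hospital phase, and remodelling is a stated objective. A scan taken late in that phase cannot be its starting point, and a missed baseline cannot be recovered.

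The 30CST raises a related but smaller question. If the first test really took place at ICU discharge, it could follow one intervention-only session.

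**Working it through.** **1. Reproduce the protocol's dose targets.** The dose per STEP is the upper session time × METs (Appendix B):

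- STEPs 1–4: 5×2, 10×2, 15×2, 15×2 = 10 + 20 + 30 + 30 = 90 MET-min. This matches "The aim of the protocol is to achieve an accumulated 90 MET-min until ICU discharge".
- STEPs 5–8: 15×3, 15×3, 20×3, 20×3 = 45 + 45 + 60 + 60 = 210 MET-min, and 90 + 210 = 300. Both match the stated ward and hospital-discharge targets.
- Doing each STEP twice would give 180 and 600, which does not match. So each STEP is done once, at two STEPs per day.

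**2. Intervention-only in-hospital dose.** STEPs 4–8: 30 + 45 + 45 + 60 + 60 = 240 MET-min, which is 240/300 = 80% of the in-hospital total. The shared STEPs 1–3 give 60.

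**3. Timeline.** Let L be the delay in days from the AMI to the first session. The protocol does not state L, so a range is assumed. STEP k falls at L + (k − 1)/2, so STEP 4 falls at L + 1.5. Let M be the elapsed days from the AMI to the scan. The fourth day can mean M = 3 or M = 4. Intervention-only MET-min delivered before the scan:

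| L | STEP 4 at | M = 3 | M = 4 | M = 5 | M = 6 |
|---|---|---|---|---|---|
| 0.5 | 2.0 | 75 | 180 | 240 | 240 |
| 1.0 | 2.5 | 30 | 120 | 240 | 240 |
| 1.5 | 3.0 | 0 | 75 | 180 | 240 |
| 2.0 | 3.5 | 0 | 30 | 120 | 240 |
| 2.5 | 4.0 | 0 | 0 | 75 | 180 |
| 3.0 | 4.5 | 0 | 0 | 30 | 120 |

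The first row puts STEP 4 at 48 hours. That is the earliest point consistent with a first evaluation after 48 hours and with HRV and 30CST before randomisation, if ICU admission is taken as close to the AMI. For example, at M = 3 STEPs 4 and 5 are done (30 + 45 = 75), and at M = 4 STEPs 4–7 are done (30 + 45 + 45 + 60 = 180).

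**4. When would the scan come first?** The scan precedes or coincides with STEP 4 only if L ≥ M − 1.5. That means a delay of 1.5 or 2.5 days for a day-4 scan (M = 3 or 4), 3.5 days for M = 5, and 4.5 days for M = 6.

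**5. Slower progression.** At one STEP per day with L = 1, STEP 4 falls at day 4 and STEP 5 at day 5. The exposure before scans at M = 4, 5 and 6 is then 0, 30 and 75 MET-min.

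**6. Share of the whole programme.** Home walking (Appendix C) adds 300 + 375 + 450 + 525 = 1,650 MET-min. So 240/(240 + 1,650) = 240/1,890 ≈ 13%.

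**7. First 30CST.** STEPs 1–3 total 60 MET-min, so the 90 MET-min target by ICU discharge includes STEP 4. A test at ICU discharge would then follow one intervention-only session (30 MET-min). But STEP 4 needs the test result to set its load, which requires a test before STEP 4. The rehabilitation section (before randomisation) and Appendix B (within STEP 3) agree with that order. Only the 30CST section says ICU discharge.

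**The case against.** The best defence is that the order of events is not fixed in the text. No day is given for randomisation or for the first session, and Figures 2 and 3 (flowchart and timeline), which could not be seen here, may settle it. The pace used is also the fastest possible: Appendix B sets clinical conditions for each STEP, the dose section allows for individual tolerance, and 8 to 10 sessions is an average. All of this stands, so the exposures are upper-end values for each assumed start.

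Several stronger readings are tempting but not supported:

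- A reader might infer that the scan certainly comes after most of the in-hospital programme. Steps 4 and 5 of the working show plausible cases with little or no prior exposure.
- A reader might infer a known bias toward no effect. The documents give no basis for the effect of one to five low-intensity sessions on MRI, and the exposure at issue is at most about 13% of the planned intervention-only dose.
- A reader might object to adjusting for a post-randomisation covariate. The Statistic Strategy plans no such adjustment.
- A reader might extend the problem to the VO2 comparison or to HRV. CPET is compared between groups without a baseline, and HRV is explicitly measured before randomisation, so neither is affected.
- A reader might conclude that the first 30CST is a treated baseline. Most of the text points to a test before STEP 4, so this is a wording conflict.

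The core remains. The protocol ties HRV to before randomisation and does not do so for MRI, while analysing both as PRE-CR.

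**Conclusion.** The point holds as a likely, not certain, defect in the MRI baseline. With STEP 4 at 48 hours and two STEPs a day, 75–180 of 240 intervention-only MET-min (31–75%) precede a day-4 scan, and all 240 precede a scan at 5 or 6 elapsed days. Avoiding any prior exposure needs a first session delayed by about 1.5–2.5 days or more for a day-4 scan, and longer for a later one. This rests on the assumed start delay, on advancing one STEP per session, and on randomisation coming no later than STEP 4, which the text implies.

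The consequence is limited but real. Within-arm MRI change omits any effect already present at the scan and cannot evaluate the in-hospital phase. A between-arm comparison of follow-up MRI values would not suffer from this. For the 30CST, the finding is only that the passages conflict. Severity: should fix.

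**What to change.** 1. Define baseline, for every outcome that has one, as the last value before randomisation, and state when randomisation occurs relative to STEP 4.
2. State that the first 30CST is done before randomisation. Correct the ICU-discharge wording in the 30CST section, and align it with the rehabilitation section, Appendix B and the 48-hour statement in Data collection procedures.
3. For MRI, choose one option:
   - Scan before the first intervention-only session, where feasible. This may move the scan ahead of its day 4–6 window, so it is a scheduling change and not merely an edit.
   - Keep day 4–6, but call it an early post-randomisation measurement, do not use it as PRE-CR, and compare follow-up MRI between arms. Adjustment is optional and, with 24 patients, should be limited to one pre-randomisation variable already on the Appendix A form. Candidates are echocardiographic EF, which is probably a weak covariate because entry requires EF above 50%, or peak troponin or CPK if the peak is recorded before randomisation.

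Items 1 and 2 cost only wording. The second MRI option needs no change of schedule. Its price is the loss of a true MRI baseline, which means less precision and no pre-treatment change score.
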